## Abstract

Despite an estimated 2.8 million annual ED visits, traumatic brain injury (TBI) is a syndromic diagnosis largely based on report of loss of consciousness, post-traumatic amnesia, and/or confusion, without readily available objective diagnostic tests at the time of presentation, nor an ability to identify a patient's prognosis at the time of injury. The recognition that “mild” forms of TBI and even sub-clinical impacts can result in persistent neuropsychiatric consequences, particularly when repetitive, highlights the need for objective assessments that can complement the clinical diagnosis and provide prognostic information about long-term outcomes. Biomarkers and neurocognitive testing can identify brain injured patients and those likely to have post-concussive symptoms, regardless of imaging testing results, thus providing a physiologic basis for a diagnosis of acute traumatic encephalopathy (ATE). The goal of the HeadSMART II (HEAD injury Serum markers and Multi-modalities for Assessing Response to Trauma) clinical study is to develop an *in-vitro* diagnostic test for ATE. The BRAINBox TBI Test will be developed in the current clinical study to serve as an aid in evaluation of patients with ATE by incorporating blood protein biomarkers, clinical assessments, and tools to measure, identify, and define associated pathologic evidence and neurocognitive impairments. This protocol proposes to collect data on TBI subjects by a multi-modality approach that includes serum biomarkers, clinical assessments, neurocognitive performance, and neuropsychological characteristics, to determine the accuracy of the BRAINBox TBI test as an aid to the diagnosis of ATE, defined herein, and to objectively determine a patient's risk of developing post-concussive symptoms.

## Background

Mild traumatic brain injury (mTBI) annually affects over 23 million people worldwide (1). In 2014, there were an estimated 2.5 million TBI-related emergency department (ED) visits in the US, of which 90% were estimated to be the result of mTBI (2, 3). From 2006 to 2014, the number of TBI-related ED visits increased by 53% (4), although the real incidence is likely much higher, as mTBI is underdiagnosed in the ED (5, 6), patients may present to alternate venues (e.g., primary care), or they do not seek care at all. The majority of adults over age 40 report a history of head injury with loss of consciousness at some point in their lives (4, 7–9).

Over 90% of TBI is classified as “mild” TBI, a term that has been criticized as misleading, since many of these injuries result in significant disabilities (10), especially if they are repetitive (11). Despite a classification of “mild,” TBI can cause persistent cognitive and physical symptoms with major impacts on affected patients function and quality of life (12, 13). In 2010 an estimated 2% of the U.S. population lived with TBI-related disabilities, at an annual estimated expense of about $77 billion (4).

Despite the magnitude of this global public health problem, the diagnosis and classification of mTBI remains challenging. The terms mTBI and concussion (which has no accepted standard definition) continue to be used interchangeably, with a 2014 review reporting 50 different mTBI definitions across 101 studies (14). Although the NINDS have developed TBI common data elements (15), the lack of objective diagnostic or prognostic tools for mTBI severely limits its effectiveness.

To date, few U.S. Food and Drug Administration (FDA) cleared strategies are available to objectively diagnose, or define prognosis, in patients presenting with head injury. While anatomic imaging methods, generally with computerized tomography (CT), show TBI-related abnormalities in ~10% of patients evaluated in EDs, a significant number of patients have disabling TBI symptoms despite initial negative imaging. When neuroimaging is negative, there are few currently available objective tests to identify significant occult injury and predict future dysfunction. Consequently, while acute care physicians can exclude emergencies that require neurosurgical intervention, or neurocritical care (e.g., intracranial hemorrhage) by imaging or physical examination, and they can perform testing to exclude the need for imaging (16), they have limited ability to objectively diagnose mTBI or identify which patients will suffer longer term poor outcomes. In fact, one ED study demonstrated that the ability of physicians to prospectively identify patients who will have subsequent mTBI related symptoms 90 days after their presentation is extremely poor, with a sensitivity of only 8.1% and a specificity of 54.5% (17).

Diagnosis of mTBI in the ED is currently based on clinical findings, which can be problematic, since the medical history is often incomplete, symptoms are vague, and the physical signs are non-specific. These challenges are further confounded by factors such as intoxication or pre-existing neurologic impairments (18). The recent availability of biomarker testing may allow for more precise identification of patients with mTBI, as a manifestation of acute traumatic encephalopathy (ATE), by adding the objective evidence of injury-related leakage of brain-derived proteins into the blood (16). Although ATE testing is currently unavailable in the acute care environment, the ATE cohort is identified as having abnormal biomarkers and/or neurocognitive dysfunction, irrespective of the results of neuroimaging. Ultimately, this strategy may be applied to risk stratify patients by determining their likelihood of developing downstream symptoms caused by their TBI.

In addition to biomarkers, evidence also supports the value of adding neurocognitive (NC) assessments for the characterization of functional deficits at the time of injury (19). The use of NC testing to identify patients at risk for protracted or disabling neurological deficits following head injury, irrespective of an imaging evaluation, may allow the selection of patients who will benefit from targeted interventions that have the potential to improve patient outcomes (20–24).

BRAINBox TBI Test is a novel technology that uses a multi-marker serum panel, in conjunction with computerized neurocognitive testing, to aid in an objective diagnosis of ATE. In addition, results of this testing strategy may identify those at risk for of persistent symptoms, i.e., it provides a prognostic determination. Thus, our purpose is to determine the ability of BRAINBox TBI Test technology to identify patients with ATE, as well as to define their prognosis, in real-world patients presenting with suspected ATE.

## Methods

Our primary objectives are to determine the ability of the BRAINBox TBI Test to:

Diagnose ATE using statistical modeling methods that combine blood biomarker values, focused patient health information, and NC/NP testing.Predict persistent symptoms up to 90 days after a diagnosis of ATE by using statistical modeling combining biomarkers, focused patient health information, and NC/NP testing.

HeadSMART II (HEAD injury Serum markers and Multi-modalities for Assessing Response to Trauma) is a clinical study that was devised to provide the information for these objectives and to provide clinical validation of the test. This is a multicenter, international, observational study, NCT04423198, with an expectation of enrolling up to 2000 subjects. The study started Q1 2021, with enrollment anticipated to be completed by the end of 2022. Subjects include those with suspected ATE, and control populations. Inclusion and exclusion criteria are provided in Table 1. Data compliant with Common Data Elements; Modular Data Elements for Traumatic Brain Injury (25), as well as ICD codes, will be collected at the index visit (*t* = 0), and at 14-, 30- and 90-days post-injury in suspected ATE patients, at the index visit and at 14 days for trauma control patients, and only at the index visit for healthy control subjects. All participants will provide 2 blood draws (separated by 1–4 h) and NC assessments at enrollment, and with added symptom specific assessments and neuropsychological testing (patient reported outcomes, PROs) at their follow up visits. Blood draws will consist of obtaining serum, plasma (including optional collection for DNA analysis) and PAXGene tubes, which are processed according to manufacturer's recommended protocols, then stored at −80C, and shipped to a core lab for biomarker analysis. Biomarker analysis will use BRAINBox's proprietary serum/plasma biomarker assays including, but not limited to, GFAP (Glial Fibrillary Acidic Protein), NSE (Neuron Specific Enolase-2), NRGN (Neurogranin), SNCB (Beta-Synuclein), and MT3 (Metallothionein-3). These biomarkers were chosen due to their demonstrated diagnostic and prognostic utility for TBI in the HEADSMART pilot trial (26–30).

**Table 1 T1:** Inclusion and exclusion criteria.

**A. Inclusion Criteria: Suspected ATE subjects**
1. Presents with a blunt head trauma
2. Age ≥ 18 years, and ability to provide a blood sample within 96 h of injury
3. Ability to provide informed consent. Consent may be obtained with assistance of a legally authorized representative (LAR)
4. Presents with a blunt head trauma
**B. Exclusion Criteria: Suspected ATE and Trauma Control subjects**
1. Glasgow Coma Scale (GCS) score <13, at time of screening
2. Need for general anesthesia at the time of presentation in the ED
3. Diagnosed dementia requiring assistance for daily living
4. Any head trauma requiring medical attention from a physician within the last 6 months
5. Received chemotherapy or radiation within the last year
6. History of stroke with disabling outcomes, brain tumor, epilepsy or intracranial surgery/hemorrhage
7. Psychiatric hospitalization in the last 90 days
8. Blood transfusion within the prior 4 weeks
9. Non-working telephone number
10. Current participant in an interventional clinical trial
11. Cannot perform study tasks on an iPad (e.g., not wearing corrective lenses necessary to read, inability to use both hands)
12. Subject unsuitable for participation, as determined by their physician, or any research staff
**C. Inclusions for Trauma and Healthy Controls**
1. Age ≥ 18 years
2. Ability to provide a blood sample; (For Trauma Controls within 96 h of injury)
3. Ability to provide informed consent. (For Trauma Controls consent may be obtained with assistance of a legally authorized representative)
4. Presents with at least one injury requiring an X-Ray (TC's only)
**D. Exclusions for Healthy Controls (HC's)**
1. Head trauma or symptoms with head trauma at presentation
2. Head trauma requiring medical attention from a physician within the last 6 months
3. Internal organ injury that requires inpatient hospitalization
4. Need for general anesthesia at the time of presentation in the ED
5. Diagnosed dementia requiring assistance for daily living
6. Received chemotherapy or radiation within the last year
7. History of stroke with disabling outcomes, brain tumor, epilepsy or intracranial surgery/hemorrhage
8. Psychiatric hospitalization in the last 90 days
9. Blood transfusion within the prior 4 weeks
10. Non-working telephone number or participant in an interventional clinical trial
12. Cannot perform study tasks on an iPad (e.g., no glasses necessary to read)
13. Subject considered unsuitable for participation by physician, or any research staff

The blood biomarker values are quantified by comparing the raw signal detected from replicates to a calibrant curve that covers a concentration range greater than the clinical range of the samples tested. The replicates are evaluated for specifications including coefficient of variation that determine the technical validity of the test. All samples passing acceptance criteria are reported as a quantity (amount per unit volume, e.g., picograms/milliliter). The biomarker values will be used as predictors in the statistical/machine learning algorithms.

The BrainCheck Application will be used to provide digitized neurocognitive assessments at each visit, the details of which are given in Table 2. BrainCheck uses digitized versions of several previously validated neurocognitive pen and paper tests, each with associated metrics of function such as duration and accuracy of responses. These comprise a composite battery and that also includes measures of balance and coordination, functions that can be affected by acute brain injury. For each subject, the data are compared against a normative/reference database previously developed by BrainCheck. The normalized values will also be used as predictors in the statistical/machine learning algorithms.

**Table 2 T2:** Neuropsychiatric/neurocognitive testing (19).

**Tests for ATE Score and Prognosis Report**
a. Rivermead (collected on BrainCheck iPad)
b. BrainCheck Cognitive Assessments
i. Flanker Test
ii. Trail Making Test A and B
iii. Digit Symbol Substitution Test
iv. Stroop Test
v. Recall Test
vi. Coordination/Balance Test
**Additional Neurological Tests for use in Prognosis Report**
a. Headache Impact Test (HIT-6)
b. Dizziness Handicap Inventory
c. Convergence Insufficiency Symptom Survey
d. Balance Error Scoring System (BESS)

The clinical data are collected through electronic CRFs and stored in REDCap Cloud Electronic Data Capture software. The NINDS common data elements for general reporting and for traumatic brain injury have been used to guide the design of the study and the CRFs.

Subjects participate in the study for up to 90 days, must enroll within 96 h of blunt head trauma, and have a Glasgow Coma Scale ≥13 at presentation. Up to 1,600 suspected ATE subjects will be enrolled through the study time points to provide sufficient subjects for separate algorithm training and validation cohorts. The demographic breakdown of the subjects will meet good clinical practice guidelines (31). For the determination of prognosis, subjects are first adjudicated as positive for TBI by a diagnostic adjudication committee, who provide an expert clinical diagnosis after reviewing the complete patient history and assessment up to 1-month post-injury. Diagnosed TBI subjects will be further categorized by the presence of symptoms at each study time point.

The Diagnostic Adjudication Committee (DAC) will consist of a panel of physicians experienced in the diagnosis and management of TBI. Two adjudicators, blinded to BRAINBox TBI Test results, will be randomly selected to review each subject's de-identified medical records, physical examination notes, neurological assessments (see Table 2), and core lab neuroimaging report, to define an expert clinical diagnosis of “TBI” or “no TBI.” The adjudication process will begin with each group after the participants have completed their respective follow up visit(s). The expert clinical diagnosis is obtained when 2 panel member's independent diagnoses agree. In the case of diagnostic disagreement, a third panel member performs an independent record review and serves as the tie breaker.

For participants who receive a head CT or MRI as part of standard care, their images are recorded and reviewed by a core lab. The neuroimaging core lab consists of a panel of board-certified neuro-radiologists, two of whom read all images and provide a report to the diagnostic adjudication committee. If the 2 readers do not agree, a 3rd will serve as a tie breaker to define the final report.

Control subjects will be enrolled for the purposes of assay development, including establishing the biomarker reference intervals, and will be cohorted into groups based on age and sex. These will include 120 trauma controls through 14 day follow up, and 120 healthy controls with a single visit. Trauma controls are defined as patients presenting to the ED for a traumatic injury and requiring an X-ray, but who do not have head trauma. Healthy controls will be subjects that report to be healthy and are not taking any prescription medications.

The BRAINBox TBI Test results determining a diagnosis of ATE, will be compared to the expert clinical diagnosis. Adjudicated patients assigned a diagnosis of TBI will be stratified for having high or low risk for post-concussive symptoms in each symptom category, based on biomarker and neuropsychiatric testing, and are defined as either “ATE with” or “ATE without” post-concussive symptoms. The high or low risk for post-concussive symptoms in each symptom category is defined using the validated interpretation guides for each test (Table 3), relevant literature with input from Key Opinion Leaders.

**Table 3 T3:** Symptom categories with corresponding neurocognitive and neuropsychological tests.

**Neuropsychological/ Neurocognitive Test**	**Symptom Category**
Headache Impact Test (HIT-6)	Headache
Dizziness Handicap Inventory, Convergence Insufficiency Symptom Survey, Balance Error Scoring System (BESS)	Motor Impairment (Balance, Dizziness/Vertigo, Visual Dysfunction)
Patient Recorded Outcome Measurement Information System (PROMIS), Sleep Disturbance Short Form	Sleep Disturbance
Glasgow Outcome Scale-Extended (GOSE-E), BrainCheck	Cognitive (Memory, Attention, Concentration, Executive Function)
Generalized Anxiety Disorder (GAD-7), Post-traumatic Stress Disorder Checklist for DSM-5 (PCL-5), Patient Health Questionairre-9 (PHQ-9), and Perceived Stress Scale	Psychological (Depression, Anxiety, Mood, Irritability, Post-traumatic Stress Disorder PTSD)

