The performance of a prognostic ATE test will be determined by evaluating the biomarker values, neurocognitive assessments, and baseline demographics at the index visit, as predictors of 3 separate models that assign high or low risk to a subject for subsequent symptom occurrence at 14, 30, and 90 days. Symptom categories and tests performed during the study are provided in Table 3. Symptoms are evaluated as a composite at each time point, with thresholds to stratify subjects defined based on the scoring system/scale for each assessment, identifying the subject's risk for a specific symptom category at each time point. A separate statistical/machine learning algorithm will be developed for each time point that calculates the risk at the specific time after injury. In the algorithm, the definition of high or low risk for having post-concussive symptoms is defined by the decision threshold that produces the minimum sensitivity and specificity of 85 and 75%, respectively. For the validation process, the finalized algorithms will be applied to the subject's biomarker values, NC assessments, and baseline demographics (age and sex) at the index visit. If the output of the algorithm exceeds the identified decision threshold, the subject will be classified as high risk. Otherwise, the subject will be classified as low risk for post-concussive symptoms at the specified time point. The prognostic report is designed to aid the clinician in determining the subject's risk of having post-injury post-concussive symptoms at 14, 30, and 90 days.

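### Prognostic models are trained and validated only in subjects adjudicated TBI on data up to 1 month, so 14- and 30-day outcomes can influence entry and the set cannot be identified at the index visit

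*Protocol article*

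**What the plan says.** All references are to the protocol article.

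- **Entry to the prognosis set** (Methods, text after Table 2): "For the determination of prognosis, subjects are first adjudicated as positive for TBI by a diagnostic adjudication committee", that is, a committee "who provide an expert clinical diagnosis after reviewing the complete patient history and assessment up to 1-month post-injury". Adjudication starts only once the follow-up visits are complete. Subjects diagnosed with TBI are then classified by symptoms at each time point. The text before Table 3 repeats that the risk stratification applies to patients adjudicated TBI.
- **What adjudicators see** (same place): besides medical records, "physical examination notes, neurological assessments (see Table 2), and core lab neuroimaging report". They are blinded to BRAINBox results. No rule withholding 14- or 30-day symptoms is stated.
- **Outcome** (Algorithm Training and Testing): three separate models for "subsequent symptom occurrence at 14, 30, and 90 days", applied to index-visit biomarkers, neurocognitive results, age and sex.
- **Aim**: the second primary objective (Methods) is to "Predict persistent symptoms up to 90 days after a diagnosis of ATE". The last paragraph of Background gives the purpose as diagnosis and prognosis in patients who come in with suspected ATE.
- **Size** (Prognosis of ATE): 236 subjects with the target condition plus 157 without, 393 in total. At 50% ATE prevalence this becomes 786 blunt head trauma subjects for training and 786 for validation.

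**The concern.** The label that admits a subject to the prognostic analysis is assigned with the 14- and 30-day assessments in view, and symptoms at those visits are then the outcomes to be predicted. If persisting symptoms make a TBI verdict more likely, symptomatic subjects enter more readily than those who recovered quickly. The set would then hold more symptomatic subjects than the patients to whom the index-visit models are meant to apply.

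The label also does not exist at the index visit. A clinician with a prognostic result in hand cannot know whether the patient belongs to the population in which it was validated. Prognosis is one of two primary objectives, and the restriction applies in both training and validation, so it bears directly on what the prognostic claim can conclude.

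**Working it through.** **1. The sample size confirms the entry rule.** An exact one-sample binomial test with null 0.85, alternative 0.78, two-sided alpha 0.05 and power 0.80 first reaches 80% power at n = 236, as stated. Then 236 / 0.60 = 393, 393 × 0.40 = 157, 393 / 0.50 = 786 and 2 × 786 = 1,572, stated as up to 1,600. The division by 0.50 makes sense only if the ATE half alone enters the prognostic models. The article calls the 157 subjects without ATE, but as 40% of the 393 they must be ATE subjects without symptoms.

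**2. Overlap between adjudication evidence and outcomes.** Table 3 lists 11 instruments. Five are also in Table 2, which the adjudicators see: HIT-6 (headache), the Dizziness Handicap Inventory, the Convergence Insufficiency Symptom Survey and BESS (motor), and BrainCheck (cognitive). Three of five symptom categories therefore share a named instrument; sleep and psychological do not. The 1-month window covers the 14- and 30-day visits but not day 90.

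**3. Membership at the index visit.** Inputs: sensitivity 0.85, specificity 0.75, prevalence 0.50, 786 subjects (393 TBI, 393 not).

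- True positives: 393 × 0.85 = 334
- False positives: 393 × 0.25 = 98
- Test-positives: 334 + 98 = 432, of whom 98 / 432 = 22.7% are outside the prognosis set
- Test-negatives inside the set: 393 × 0.15 = 59, which is 15% of 393

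The share outside, 0.25(1 − prev) / [0.85 prev + 0.25(1 − prev)], is 40.7% at 30% prevalence and 11.2% at 70%.

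**4. Possible shift in prevalence and PPV (illustration).** From the plan: 60% symptomatic inside the set, 50% adjudicated TBI, sensitivity 0.85, specificity 0.75. Assumed: the odds ratio (OR) between symptoms and a TBI label.

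- Odds of symptoms in no-TBI subjects: (0.60 / 0.40) / OR, giving proportion q
- Prevalence in all suspected subjects: p = 0.5 × 0.60 + 0.5 × q
- PPV = 0.85p / [0.85p + 0.25(1 − p)]; NPV = 0.75(1 − p) / [0.75(1 − p) + 0.15p]
- Prevalence in test-positives: 0.773 × 0.60 + 0.227 × q, assuming the test result is unrelated to symptoms given TBI status

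| OR | q | p, all suspected | PPV | NPV | p, test-positives | PPV, test-positives |
|---|---|---|---|---|---|---|
| 1 | 0.600 | 0.600 | 0.836 | 0.769 | 0.600 | 0.836 |
| 2 | 0.429 | 0.514 | 0.783 | 0.825 | 0.561 | 0.813 |
| 4 | 0.273 | 0.436 | 0.725 | 0.866 | 0.526 | 0.790 |
| 8 | 0.158 | 0.379 | 0.675 | 0.891 | 0.500 | 0.772 |

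The odds ratio mixes two things: TBI genuinely causing symptoms, and symptoms swaying the verdict. The table therefore sizes the gap between the analysed set and all suspected subjects, not the second component alone. At OR 1 nothing shifts.

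**5. Sensitivity and specificity.** Both condition on the outcome. Selection that depends on the outcome alone leaves them unchanged. They move only if, among subjects with the same symptom status, the model behaves differently in those labelled TBI and those not. The article gives nothing that fixes the direction.

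**The case against.** The strongest defence is that restricting prognosis to TBI is deliberate. The target is post-concussive symptoms in ATE, and a high anxiety or depression score in someone without TBI is not clearly such an outcome. Follow-up information can also improve a reference diagnosis. Both points stand: the choice of population is legitimate, and the adjudicated-TBI result deserves reporting. They do not justify letting a label made with 14- and 30-day data gate the prediction of 14- and 30-day symptoms while the model is applied at the index visit.

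The overlap is also partial. Adjudicators answer TBI or no TBI, not symptom status, and six of the 11 outcome instruments are not in Table 2. The exact visit-by-visit material may be set out in the full protocol. This limits the likely strength of the effect, but the stated window still includes both visits.

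Three stronger readings are tempting and are not supported:

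- *That 23% of report recipients are left out of validation.* No text names test-positive patients as the recipients. The objective speaks of prognosis after a diagnosis of ATE, and Background of patients with suspected ATE.
- *That sensitivity and specificity are shown to be distorted.* Step 5 shows only that they could be.
- *That the 90-day model is selected directly on its outcome.* Adjudication starts after follow-up, but the stated evidence stops at 1 month, so day 90 is linked only through its correlation with earlier symptoms.

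**Conclusion.** The concern holds in a limited form. As written, entry to the prognostic set can depend on the outcomes of the 14- and 30-day models, and the set cannot be identified when those models are used. Symptom prevalence and PPV may be overstated relative to patients presenting with suspected ATE. The size is unknown: under assumed odds ratios of 1 to 8, PPV in all suspected subjects lies between 0.836 and 0.675, while NPV would rise from 0.769 to 0.891, with sensitivity and specificity held at the plan's values.

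The mismatch in membership (98 of 432 test-positives outside the set, 59 of 393 in it test-negative) follows from the plan's own accuracy and prevalence. Its practical weight depends on who receives the report. If the report went to every suspected case, half of the recipients would be unrepresented. The sample-size arithmetic is not in error on this point.

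**What to change.** Before validation unblinding, prespecify that the finalised 14-, 30- and 90-day models are validated in a set defined by index-visit information: all suspected-ATE subjects in the validation cohort, with observed symptom status as the outcome. Also report the subset classified as ATE by the BRAINBox test at the index visit. Keep the adjudicated-TBI analysis as a separate result, with its claim limited to patients later confirmed as TBI. State who is meant to receive the prognostic report.

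**Cost.** No new data are needed, since all suspected-ATE subjects are already followed to day 90. In 786 subjects, 236 symptomatic requires a prevalence of 236 / 786 = 30%, and 157 without symptoms requires that no more than 629 / 786 = 80% be symptomatic.

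The test-positive subset may fall short of 236 symptomatic subjects:

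- 50% symptomatic in TBI, 30% in no TBI (assumed): 334 × 0.50 + 98 × 0.30 = 196
- 60% (plan) and 30% (assumed): 334 × 0.60 + 98 × 0.30 = 230
- 60% in both: 432 × 0.60 = 259

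Its precision should therefore be stated. At sensitivity 0.85, the 95% half-width 1.96 × √(0.85 × 0.15 / n) is 5.0 percentage points at n = 196 and 4.6 at n = 236.

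**Downside.** Reported prognostic performance, PPV in particular, may be less favourable, and symptoms in subjects adjudicated no TBI may not be injury-related. Making test-positives the only primary set, or adjudicating again on index data alone, would be a further trade-off or an added procedure and is not required here.
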